### Severe adverse reactions

The LPS Adsorber is a class IIa medical device and does not include any drugs or toxic substances that enter the blood circulation. All components in the LPS Adsorber are biocompatible. The capturing-peptide component is nontoxic, and cannot be released during rinsing or therapy procedures as it is covalently bound to the matrix. The LPS Adsorber is part of an extracorporeal hemoperfusion system which is supplied sterile and only for single use.

All serious adverse events and serious adverse device effects are promptly reported by the investigation site to Clinical Drug Safety Support at the contract research organization (TFS Trial Form Support AB, Lund, Sweden) within 24 h of learning about the event, regardless of the time that may have elapsed from the time the event occurred and these will be evaluated and recorded.

### Amendments

Protocol amendments will be made by the Steering Committee and submitted to the ethical boards in each participating country for approval. The protocol presented is version 5 from 2 March 2016.

### Acquisition of data

An eCRF (electronic Case Report Form) system will be used. Data validation and data queries will be handled by the contract research organization‘s Data Management Team (TFS Trial Form Support AB, Lund, Sweden).

### Data handling and record keeping

A monitor from the contract research organization (TFS Trial Form Support AB, Lund, Sweden) will perform monitoring activities at the assigned clinical investigational site(s) in accordance with the monitoring plan. Management and storage of data will be handled by the contract research organization.

### Data ownership and publication policy

The investigators and the sponsor will be joint owners of all materials and all results. Any publication shall be subject to the prior review and approval of the sponsor, such approval is not to be unreasonably withheld. The sponsor shall not have a right for veto in any correct factual part of any planned publication.

### Statistics

#### Power calculation

Since this is a pilot study, no sample size calculation was possible or has been performed. The sample size was chosen for practical reasons, and aimed to allow recruitment of all subjects in the first enrollment period (i.e., stratum A and stratum B) within a year, and within six additional months for subjects in the second enrollment period. Data from this pilot investigation will provide information for designing future studies with the LPS Adsorber.

#### Endpoints

No primary performance variables will be collected in the present clinical investigation. The statistical analyses of secondary endpoints will be descriptive.

#### Analysis sets

The following analysis sets will be used for the statistical analysis:

The Full Analysis Set (FAS) will consist of all randomized subjects who were treated with the investigational device or placebo device for at least 2 h on day 1.

The Per Protocol Set (PPS) will consist of subjects from the FAS who completed at least 2 h of therapy with the investigational device or the placebo device on day 1 and on day 2. Additionally, the subjects in the PPS will not have any major CIP violations that will affect the evaluation. Major CIP violations will include but are not limited to the following:Nonfulfillment of all inclusion criteriaFulfilling at least one exclusion criteria

The FAS is considered as the primary analysis dataset, and will be used for all performance analyses. The analysis(es) that will be repeated using the PPS will be further described in the SAP. Major discrepancies between the results from the FAS and the PPS analyses will be compared and discussed.

The Safety Set will consist of all randomized subjects who started therapy. Safety summaries will be performed on the Safety Set.

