### Intervention

Upon enrollment (i.e., pre-treatment phase), subjects admitted to the ICU with suspected endotoxemia will be screened for fulfillment of the “Illness severity criteria” confirming the early stages of severe sepsis. Within 6 h of enrollment, subjects who also fulfill the “Treatment criteria” confirming septic shock will be eligible for randomization. Randomization to either of the treatment groups will be performed as close as possible to the start of treatment with the LPS Adsorber or placebo device.

Treatment with the LPS Adsorber or placebo device must be initiated within 6 h (day 1) following fulfillment of the “Treatment criteria” and given for 6 h. A second device treatment will be performed 24 h after the end of the first device treatment on day 2, as long as there is no evidence that treatment with the investigational device will not be beneficial or will indicate an unnecessary risk for subjects (for example, if the subject is free of vasopressor support).

The treatment with the LPS Adsorber or placebo can be discontinued at any time on the decision of the attending physician. At least one 2-h treatment session is required to fulfill the treatment protocol.

After treatment with the LPS Adsorber or placebo is finalized (post-treatment phase), subjects will be monitored until they are ready for ICU discharge or deceased. Discharge from hospital and mortality at 28 days since enrollment will also be collected. Figure 2 and Table 1 summarize the participant timeline of the clinical investigation.

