#### Secondary endpoints

Relative change from baseline in plasma endotoxin (p-endotoxin) levels during (i.e., at 2 h) and immediately after end (i.e., at 6 h) of therapy with device, on both day 1 and day 2Monitoring of clinical outcome parameters during stay at ICU:○ Relative change from baseline in SOFA score (total and organ specific) measured once daily and up to 120 h (or time for ICU discharge, whichever comes first) after start of therapy with device○ Relative change from baseline in the monitoring of renal function○ Relative change from baseline in the monitoring of liver function○ Relative change from baseline in circulatory support○ Relative change from baseline in respiratory support○ ICU mortality○ ICU length-of-stay (LOS) up to 28 days
Monitoring of clinical outcome parameters during stay at hospital following ICU discharge:○ The total extension of renal support○ 28-day mortality○ Hospital-LOS up to 28 days
Monitoring of inflammatory response biomarkers:○ Inflammatory triggers and markers○ Acute phase protein markers○ Plasma cytokines
Determination of the molecular components extracted from blood circulation and captured in the LPS AdsorberCharacterization of all reported adverse events (regardless of attribution), adverse device effects and device deficiencies

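### The Full Analysis Set requires 2 h of day-1 treatment, so no defined set gives the clinical outcomes of all randomised subjects

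*Protocol article*

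**What the plan says.** Three sets are defined in the protocol article, under Statistics, Analysis sets.

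- **FAS:** "all randomized subjects who were treated with the investigational device or placebo device for at least 2 h on day 1". Its role is fixed in the same place: "The FAS is considered as the primary analysis dataset, and will be used for all performance analyses".
- **Per Protocol Set (PPS):** a subset of the FAS, limited to those who reached the 2-h minimum in both device sessions and had no major violations of the investigation plan.
- **Safety Set:** "The Safety Set will consist of all randomized subjects who started therapy". Its use is also fixed: "Safety summaries will be performed on the Safety Set".

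Only the choice of analyses to be repeated in the PPS is left to the SAP.

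The Intervention section says: "The treatment with the LPS Adsorber or placebo can be discontinued at any time on the decision of the attending physician". It then adds: "At least one 2-h treatment session is required to fulfill the treatment protocol". The Participant withdrawal section lists imminent surgery, imminent need of continuous renal replacement therapy, and a CT scan among the possible reasons for withdrawal.

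The Secondary endpoints section lists SOFA, organ support, ICU mortality, "28-day mortality" and length of stay as clinical outcome parameters. Adverse events, device effects and device deficiencies form a separate item.

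**The concern.** A full analysis set is normally meant to stay as close as possible to everyone randomised. Here it depends on something that happens after randomisation: staying on the device for 2 h. That duration is also the article's own minimum for fulfilling the treatment protocol, so the FAS is already an adherence-based set.

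Whether a subject reaches 2 h can depend on the clinical course (deterioration, urgent surgery, need for renal replacement) or on the device. Either can be related to outcome, and the second could differ between arms.

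The analyses are descriptive, so the raw percentages and changes by arm are the result. The Background states that the ultimate objective is to learn the size of the clinical effects as a basis for larger studies. The Methods/design section says that these patients are to be included in a later phase IIb study of outcome. A selected clinical comparison would feed both uses.

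**Working it through.** The article states no sample-size calculation, mortality rate or early-stop rate, so there is no figure of the plan's to reproduce beyond the enrolment totals. These add up: 20 + 12 = 32, and 32 + 12 = 44 with the optional extension. With 1:1 allocation in each stratum, an arm has 10 + 6 = 16 subjects, or 22 if the optional 12 are also split equally.

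**Step 1. Who is in which set**

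| Randomised subject | FAS | PPS | Safety Set |
|---|---|---|---|
| Never connected | no | no | no |
| Connected, stopped before 2 h on day 1 | no | no | yes |
| At least 2 h on day 1 only | yes | no | yes |
| At least 2 h on both days, no major violation | yes | yes | yes |

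No column holds all four rows. The FAS and PPS are both empty in the first two rows, so setting one against the other says nothing about those subjects. The Safety Set recovers the second row, but it is assigned to safety summaries.

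**Step 2. Effect of an exclusion on an arm's mortality**

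Let an arm have n randomised subjects and d deaths. Excluding k subjects who die gives (d − k)/(n − k). Excluding s subjects who survive gives d/(n − s). Assume n = 16 and d = 6:

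- all randomised: 6/16 = 37.5%
- one early death excluded: 5/15 = 33.3% (−4.2 points)
- two early deaths excluded: 4/14 = 28.6% (−8.9 points)
- one early-stopped survivor excluded: 6/15 = 40.0% (+2.5 points)
- two early-stopped survivors excluded: 6/14 = 42.9% (+5.4 points)

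If one arm lost one early death and the other lost one early-stopped survivor, two arms identical at 37.5% would appear as 33.3% and 40.0%, an apparent gap of 6.7 points.

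**Step 3. Range over the assumed number of deaths**

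| Arm | One death excluded | One survivor excluded |
|---|---|---|
| 16, with 5 to 8 deaths | −4.6 to −3.3 points | +2.1 to +3.3 points |
| 22, with 7 to 11 deaths | −3.2 to −2.4 points | +1.5 to +2.4 points |

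Examples at the ends: 4/15 − 5/16 = 26.7% − 31.3% = −4.6 points; 11/21 − 11/22 = 52.4% − 50.0% = +2.4 points.

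**Step 4. Chance that the rule excludes anyone**

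If a proportion q of subjects gets less than 2 h, the chance of at least one exclusion among 32 is 1 − (1 − q)^32. This is 62% for q = 3%, 81% for q = 5% and 97% for q = 10%. These values of q are assumptions.

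**The case against.** Several points on the other side stand.

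**Harm is not lost.** A reader might infer that early deteriorations, clotted circuits or early deaths disappear from the trial. They do not. The Safety Set has no 2-h minimum, the primary endpoint is serious adverse device effects, and adverse events and device deficiencies are separate listed endpoints. Only subjects who never start therapy fall outside the Safety Set.

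**Mortality is not expressly assigned to the FAS.** A reader might take it as settled that the mortality tables omit early deaths. The article ties the FAS to performance analyses. Its Background, when spelling out performance, names endotoxin removal, organ failure, organ support and inflammation, but not mortality. The FAS is the natural home for mortality because it is the primary dataset and mortality sits among the clinical outcomes. An SAP that is not shown could still tabulate deaths in the Safety Set.

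**The direction of bias is not fixed.** A reader might infer that the arm with more early stops must look better. That holds only if those excluded fare worse. A stop for a CT scan or a clotted circuit need not be a death, and excluding survivors moves the figure up.

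**The numbers excluded may be small.** Subjects expected to die within 24 h are not eligible, and randomisation is to be as close as possible to treatment start. Blinded cartridges mean that stopping cannot follow knowledge of the allocation. These points reduce the risk without removing it: Table 1 places randomisation at the treatment-criteria screening, up to 6 h before treatment, and an effect of the active peptide on stopping could still differ by arm.

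**Imprecision dominates.** The exact 95% interval for 6/16 runs from 15% to 65%, so one exclusion is small beside chance, and no test or decision rule in the article is shown to rest on the FAS. This argues for a lower severity. It does not justify a selected set when the complete one is easy to obtain.

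**Conclusion.** The point holds in a limited form. The FAS is not an all-randomised set, no other set fills the gap, and the planned FAS versus PPS comparison cannot reveal the consequence. What is affected is the comparison of clinical outcomes: SOFA, organ support, length of stay and, on the natural reading, ICU and 28-day mortality. The safety conclusions are not affected by the 2-h rule.

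Under the assumed death counts, each exclusion in one arm shifts that arm's mortality by about 2 to 5 points downward if the subject died, or about 2 to 3 points upward if the subject survived. How often this would happen cannot be known from the article.

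Severity is should-fix: the secondary analyses are descriptive and the primary endpoint stands, but the results are meant to inform the size of effect and to carry over into phase IIb.

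**What to change.** In the investigation plan and the SAP, define the FAS as all randomised subjects, analysed in the arm to which they were allocated, and use it for mortality, SOFA, organ support and length of stay. Keep the group with at least 2 h of treatment on day 1 as a named supplementary set for endotoxin change and adsorber-bound content, where exposure to the device is part of the question. State which set carries ICU and 28-day mortality, and report by arm how many subjects were never connected or stopped before 2 h, with reasons. Make the change before allocation is unblinded.

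**Cost.** The definitions are a short text change. Mortality, length of stay and the severity scores are already scheduled in Table 1, so the added work is outcome follow-up of the few subjects stopped early or never started, as far as consent allows. Because SOFA is timed from the start of device therapy, a time origin is also needed for subjects who never start; randomisation would serve. The all-randomised analysis will slightly dilute any treatment effect, and the supplementary set shows the undiluted device measures beside it.

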#### Interim analysis

An interim analysis will be performed after all subjects in their corresponding stratum have completed their participation in the investigation to assess whether 12 additional subjects are required.

## Discussion

To date, there is no specific therapy for the inflammatory response induced by bacteria in sepsis. Given its role in triggering inflammatory responses, endotoxin could play a central role in inducing organ failure in Gram-negative sepsis. Endotoxin removal with an endotoxin-specific, high-affinity, high-capacity adsorber system is, therefore, an attractive therapeutic option. The LPS Adsorber used in this study fulfills these characteristics.

The key goal of this study is to identify patients who might benefit from endotoxin removal. This goal is achieved by including severely ill septic shock patients with presumed endotoxemia and initiating endotoxin removal therapy early. The objective of the ASSET study is to investigate the safety and feasibility of LPS Adsorber therapy and to provide data for further studies.

### Trial status

Recruitment of patients started in September 2015.

## Abbreviations

ALT: Alanine aminotransferase
AST: Aspartate aminotransferase
CIP: Clinical investigation plan
CRRT: Continuous renal replacement therapy
CT: Computed tomography
eCRF: Electronic Case Report Form
HIT II: Heparin-induced thrombocytopenia II
ICU: Intensive care unit
IMD: Interventional Medical Device
LOS: Length-of-stay
MAP: Mean arterial pressure
RRT: Renal replacement therapy
SAPS II: Simplified Acute Physiology Score
SIRS: Systemic inflammatory response syndrome
SOFA: Sequential Organ Failure Assessment
